### Sensitivity analyses

Impact of any missing outcomes for day 14 and day 90 mortality will be assessed using imputed outcomes under best–worst and worst-best case scenarios. In the best–worst scenario, a “best” outcome event (i.e. did not die) will be assigned in place of all missing outcomes in one treatment arm, and a “worst” outcome event (i.e. died) in place of all missing outcomes in the other treatment arm. The worst-best scenario will be the opposite assignment of outcomes. If the conclusions are similar for these two scenarios, then no missing data analyses will be conducted. However, if conclusions are substantively different, then a multiple imputation analysis will be performed, where missing outcomes will be imputed using chained equations and predictive mean matching, using the five nearest neighbours, in each of the study arms.

Other sensitivity analyses including *per protocol* analysis and *as treated* analysis, based on management of MAP targets during the first 48 h of vasopressor or inotrope therapy post randomisation, will also be conducted. For per protocol analysis, those patients who were not able to be managed as per the specified protocol for the allocated arm will be excluded from each group. For as treated analysis, patients will be grouped into study arms according to the protocol of the study arm that was followed. Determinative thresholds for protocol non-compliance for the control arm will be the mean achieved MAP greater than 75 mmHg and mean MAP-deficit < 8% and mean noradrenaline-equivalent dose > 0.10 mcg/kg/min during the first 24 h of the study period. Whereas determinative thresholds for protocol non-compliance for the intervention arm will be the mean achieved MAP less than 75 mmHg and mean MAP-deficit of 8% or more and mean noradrenaline-equivalent dose < 0.15 mcg/kg/min during the first 24 h of the study period.

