### Sample size

Based on our pilot feasibility study [11] and prospective cohort study [8], a sample size of 1260 is required to demonstrate an absolute risk reduction of 6% in the primary endpoint (14-day mortality) in the intervention arm, assuming a 20% incidence of 14-day mortality in the control arm, at an alpha level of 0.05 and power of 80% and allowing for 2.5% attrition. The absolute risk difference of 6% is a conservative estimate relative to the effect size observed in our feasibility study (14-day mortality rate of 13% versus 6% in the standard care versus individualised blood pressure target) [11] or the effect size observed in a pre-specified comparative analysis in our prospective cohort study (14-day mortality rate of 13% versus 22% (*p* = 0.04) in the group with lower-than-median blood pressure deficit versus the group with higher-than-median blood pressure deficit) [8].

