### Primary outcome

Effect estimates for 14-day all-cause mortality will be derived from multivariable logistic mixed effects models with a random intercept for site (assumed normally distributed on the logit scale, with a constant variance) to account for clustering within sites and fixed effects for treatment group, time between T0 (initiation of vasopressor therapy) and randomisation, APACHE III score at randomisation, noradrenaline-equivalent dose at randomisation and type of shock (Table 4). A two-sided *P*-value for the effect of treatment will be obtained from this model and values < 0.05 will be considered statistically significant. The effect estimates of interest will be the relative risk and risk difference (individualised care versus standard care). The relative risk estimate will be obtained as a ratio of the mean for each group of the individual predicted probabilities obtained from the logistic regression model. Differences of these means will be the risk difference. Bootstrapping, using 10,000 iterations, will be used to calculate 95% confidence intervals.

**Table 4 Tab4:** Outcome measures

	Standard MAP (*n* = xxx)	Individualised MAP (*n* = xxx)	Adjusted^*^ relative risk (95% CI)	Adjusted^*^ risk difference (95% CI)	*P* value
Day 14 all-cause mortality, *n* (%)					
Major Adverse Kidney Event^δ^ within 14 days of randomisation, *n* (%)					
- New requirement for RRT					
- Doubling of creatinine					
RRT- free days^#^ by day 28, *n* (%)					
Day 90 all-cause mortality, *n* (%)					

*RRT* renal replacement therapy

^*^ The model included random intercepts for sites and fixed effects for treatment group, the time between T0 (initiation of vasopressor therapy) and randomisation, APACHE III score at randomisation, vasopressor dose at randomisation and type of shock

^**δ**^ Major adverse kidney event (MAKE)−14 was a composite outcome of death, or new renal replacement therapy during the first 14 days, or doubling of serum creatinine from pre-illness level on day 14 or on day of discharge from ICU, whichever was earlier

^#^ Patients who died were assigned the worst score of − 1

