### Missing data or incongruent data

Medical records will be used to ascertain all outcomes. Outliers will be interrogated for validity and impact explored via sensitivity analyses. The intention to treat population for the primary and secondary outcomes is all participants as randomised. It is expected that there will be no, or minimal, missing data for the outcomes. Analysis of outcomes will be complete case analysis and is expected to include the entire intention to treat population or very close to the entire population. MAP and percentage MAP deficit may be missing for some timepoints, but the method of analysis for MAP and percentage MAP deficit does not require all observations to be non-missing. Missing APACHE III score, type of shock and site data is not anticipated. The proportion of data defining the subgroups is also expected to be complete or nearly complete and patients with missing data will not be included in any subgroup analysis. To minimise loss to follow-up, each site will designate a coordinator responsible for outcome tracking, and outcome data will be obtained from hospital records or national mortality registries where required.

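### When the best-worst and worst-best mortality scenarios disagree, the only planned follow-up is an imputation that implicitly assumes missing at random, and nothing grades results between the extremes

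*Protocol article*

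**What the plan says.** The section on missing or incongruent data makes the main analysis complete case: "Analysis of outcomes will be complete case analysis". It expects few or no missing outcomes.

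The section on sensitivity analyses then sets a two-step rule for missing day-14 and day-90 mortality.

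- **Step 1.** Missing outcomes are set to survival in one arm and death in the other, and then the reverse. If the two agree, the work stops: "If the conclusions are similar for these two scenarios, then no missing data analyses will be conducted".
- **Step 2.** If they do not agree: "However, if conclusions are substantively different, then a multiple imputation analysis will be performed, where missing outcomes will be imputed using chained equations". The method is predictive mean matching with five donors, run separately by arm.

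The section names no imputation predictors, no missing-data assumption and no analysis between the two extremes. It does not say how to conclude if the scenarios disagree while the imputation agrees with complete case. The sample-size section gives the relevant scale: "assuming a 20% incidence of 14-day mortality in the control arm", an "absolute risk reduction of 6% in the primary endpoint (14-day mortality) in the intervention arm", and "allowing for 2.5% attrition".

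**The concern.** The two scenarios can disagree only if the conclusion depends on how patients with unknown outcomes fared. That is a missing-not-at-random question. Matching each missing patient to observed donors in the same arm supposes that, given the predictors, the missing patients resemble the observed ones. The follow-up therefore does not address the question that triggered it.

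What is at stake is the reading of a positive mortality result after a failed scenario check. Some such results would be overturned by a small departure from missing at random, others only by an extreme one. The planned steps give the reader no figure that separates them.

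**Working it through.** **Inputs.** From the sample-size section: 20% control mortality, a 6-point reduction (so 14%), 1260 patients, and "at an alpha level of 0.05 and power of 80% and allowing for 2.5% attrition". Allocation is 1:1 (randomisation section), so 630 per arm. The test is two-sided ("A two-sided *P*-value for the effect of treatment will be obtained from this model"). The checks below use unadjusted two-proportion z-tests with pooled variance, not the planned mixed model.

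**The plan's own figure.** n per arm = [1.96·√(2·0.17·0.83) + 0.8416·√(0.20·0.80 + 0.14·0.86)]² / 0.06² = 614.1, rounded up to 615. The total is 1230, and 1230/0.975 = 1262. The stated 1260 is reproduced to within rounding.

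**Is the branch reachable?** At 2.5%, 0.025 × 630 ≈ 16 are missing per arm and 614 observed. Observed deaths are 123 (control) and 86 (individualised). The plan does not say which arm is which, so here best-worst means the version favouring the individualised arm.

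| Analysis | Control | Individualised | Difference | P |
|---|---|---|---|---|
| Complete case | 123/614 | 86/614 | 6.0 points | 0.005 |
| Best-worst | 139/630 | 86/630 | 8.4 points | 0.0001 |
| Worst-best | 123/630 | 102/630 | 3.3 points | 0.12 |

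The scenarios disagree on significance. With the 6-point effect they still agree at 1.5% missing (worst-best P = 0.038) and disagree at 2% (P = 0.076). With a smaller but still significant effect, 20% versus 15.5%, they disagree at 0.5% missing, about 3 per arm: complete case 125/627 versus 97/627, P = 0.038; worst-best 125/630 versus 100/630, P = 0.066.

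**What does the imputation add?** Simulation of 1260 patients with 20 imputations, five donors by arm, an adjusted logistic model with standardised risk difference and no site effect. There were only 30 trials per scenario at 2.5% missing, and the covariate effects and missingness mechanisms are assumed.

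- Imputing from the primary-model covariates alone, the mean absolute gap from complete case was 0.05 to 0.09 points across four mechanisms, with the same standard error.
- Informative loss (missingness depending on the outcome, differently by arm): full data −5.6 points, complete case −7.4, imputation −7.4. With a strong auxiliary variable added, the imputation gave −6.8.
- Missingness driven by that auxiliary variable: full data −5.2, complete case −6.6, imputation using it −5.1.

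So the imputation repeats complete case when it uses no more than the analysis covariates. It can correct loss explained by an auxiliary variable, and it corrects informative loss only partly.

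**Can the rule grade results?** Take 16 missing per arm and let 3 of the 16 missing controls die (126/630), close to the observed control risk. Increase deaths among the 16 missing individualised patients until significance is lost.

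| Observed deaths | Complete-case P | Worst-best P | Last significant | Lost at |
|---|---|---|---|---|
| 123/614 v 86/614 | 0.005 | 0.12 | 13 of 16 (P = 0.047) | 14 of 16 (P = 0.056) |
| 123/614 v 95/614 | 0.037 | 0.38 | 4 of 16 (P = 0.047) | 5 of 16 (P = 0.056) |

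In odds terms, the first tips when missing individualised patients have (14/2)/(86/528) ≈ 43 times the observed odds of death. The second tips at (5/11)/(95/519) ≈ 2.5 times. Best-worst is significant in both (P = 0.0001 and P = 0.0014), so both fail the scenario check and both go to the same imputation.

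**The case against.** The strongest reply has four parts.

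1. **The scenarios are themselves not-at-random analyses, at the limits.** Agreement shows robustness to any pattern of missing outcomes, and disagreement shows sensitivity to the extremes. This stands. A reader might infer that the rule cannot tell a robust result from a fragile one, or that a fragile result will be called robust. The document does not support that: nothing says the imputation overrides the scenarios, that they go unreported, or that the result is then declared robust.

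2. **The imputation predictors are not named.** A reader might infer that the imputation must reproduce complete case by construction. That holds only if it uses no more than the primary-model covariates. The trial records lactate, creatinine, ventilation and serial MAP, among others, and a strong auxiliary variable did move the estimate. This also stands, but under informative loss it moved only part of the way, and the article commits to no such variable.

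3. **Missing deaths should be rare.** The 2.5% is a sample-size allowance. The article expects minimal missingness, assigns a coordinator at each site to track outcomes, and draws on hospital records and mortality registries. This limits the weight of the point. It does not remove it, because an effect near the significance threshold can trigger the branch at 0.5% missing.

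4. **A further sensitivity analysis is a preference, and such detail may sit in a supplement that is not shown.** Predictor lists can fairly be left there. The two-step rule itself, however, is stated in the article, and its second step is poorly matched to its trigger.

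**Conclusion.** The concern holds in a limited form. After a failed scenario check, the stated follow-up does not address the not-at-random question that triggered it, and no graded analysis lies between the extremes. At the plan's own 2.5% attrition and 20% versus 14%, the branch is triggered (worst-best P = 0.12). Results that tip at about 2.5 times and about 43 times the observed odds of death would follow the same path.

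This rests on unadjusted tests, equal missingness by arm, reading "conclusions" as significance at 0.05, and small simulations with assumed mechanisms. That the imputation assumes missing at random is inferred from the method; the article does not use the term. If mortality is nearly complete, the practical effect is small. This is a cheap improvement, not an error that invalidates the analysis.

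**What to change.** In the sensitivity-analyses section:

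- Keep both extreme scenarios and state that both are reported, whatever follows.
- Keep the within-arm imputation as the reference point (delta = 0), and name its predictors, including any auxiliary variables.
- When the scenarios disagree, add a pre-specified tipping-point (delta-adjusted) analysis. Vary the odds of death among missing patients separately by arm, for example from 1 to 10 times the observed odds, and report the arm difference at which the primary conclusion changes, or that it does not change within the grid.
- Fix the grid before unblinding. One chosen after a discordant result would carry little weight.

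The cost is a few sentences, some analysis work and one more table, with no new data. The downside is that a positive result may have to be reported as sensitive to missing outcomes.

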### Additional analyses

If the overall intervention effect is significant in the primary analysis, additional exploratory analyses may explore whether MAP-deficit mediates the relationship between the intervention and the primary outcome. A supplementary analysis of 14-day all-cause mortality may also be undertaken within a Bayesian framework (Figure S5), since Bayesian inferences are more intuitive and are helpful in providing more context and there are increasing calls for including Bayesian analysis to complement frequentist analysis for RCTs [23, 24]. This analysis plan is described in detail in the supplement.

### Oversight and monitoring

This RCT will be coordinated by the clinical trials unit at Hunter Medical Research Institute. The trial management group comprises the chief investigator, project manager and clinical trials unit manager, who are responsible for the day-to-day conduct of the trial, including protocol compliance, site coordination and data quality monitoring. The trial steering group comprising of the chief investigator, medical co-investigators and project co-managers oversees trial governance and ensures the study is conducted in accordance with Good Clinical Practice. The trial steering group will conduct regular weekly or bi-weekly meetings. Any protocol variation will be duly approved by relevant regulatory bodies and communicated to all participating sites and collaborators.

### Data safety and monitoring board

The Data Safety Monitoring Board (DSMB) for this trial comprise of three members with scientific expertise in clinical aspects of the patient population being studied, clinical trial conduct, biostatistics and methodology, and who will serve in an individual and independent capacity, free of any professional, intellectual, financial or emotional conflicts of interest in relation to the REACT SHOCK RCT and will provide their expertise and recommendations to the REACT SHOCK investigators. The DSMB members will be objective and unbiased in their assessment of safety and efficacy data provided to them periodically during the conduct of this study.

### Dissemination plans

The trial will be presented at scientific forums and results will be published in peer-reviewed indexed medical journal/s to help disseminate the trial findings to a broad audience.

## Discussion

The aim of the proposed RCT is to determine effectiveness of a strategy, where MAP targets during vasopressor therapy for shock in ICU are individualised based on patients’ own pre-illness MAP. To date no major RCT has tested this strategy among ICU patients with shock. This pivotal trial will provide evidence to fulfil a crucial knowledge gap regarding a common and a fundamental intervention in critical care. This is an opportunity for the clinicians to support a clinical trial that aims to compare the effects of individualised blood pressure targets over standard care for patients with shock in ICU.

The information that will be generated from this research programme has the potential to influence future recommendations regarding haemodynamic management of shock in ICU. In essence, the intervention being tested in this trial is simple to deliver, requires minimal additional clinical support, and if proven effective, will have a potential for significant short-term and long-term benefits for both patients and the health care system. If shown to be beneficial, this intervention can be easily adopted in clinical practice at almost no extra cost to the health care system and has a potential to lead to significant savings. As a pragmatic trial, the range of MAP targets for both arms is well within the realm of real-world practice, while also allowing clinician’s discretion to alter MAP targets if required according to evolving clinical condition for participants.

Overall, there are consistent data from the prior studies in the REACT Shock programme [5, 7, 8, 10, 11] that indicate the need to investigate merits of individualised blood pressure targets in a high-quality RCT. This intervention is directly related to one of the vital clinical parameters and is geared towards reducing potentially unwarranted variation in the degree of blood pressure deficit accepted in standard care.

## Trial status

Current protocol version 4.1 dated 27 March 2024. The trial is actively recruiting and is anticipated to complete recruitment in 2028.

## Data Availability

Not applicable
